### Frequency and plans for auditing trial conduct {23}

The study monitor will visit the study center after enrollment of every 4 patients and after each 6-month interval.

### Plans for communicating important protocol amendments to relevant parties (e.g., trial participants, ethical committees) {25}

All substantial protocol amendments will be detailed in writing and consequently sent to TUKIJA (National Committee on Medical Research Ethics) and FIMEA (Finnish Medicines Agency) via the EU C-TIS Portal. If other administrative changes need to be made to the protocol, the study will be discontinued until it receives subsequent approval by TUKIJA and FIMEA.

## Dissemination plans {31a}

The findings of this study will be presented in peer-reviewed journal publications as well as conference presentations.

## Discussion

In this Xe-SAH protocol, we describe how we intend to conduct a prospective, multicenter phase II clinical drug trial. The study design is a single-blind, randomized two-armed parallel follow-up study. The primary objective of the study is to explore the potential neuroprotective effects of xenon, when administered within 6 h after the onset of symptoms of aSAH. Due to the devastating nature of an aSAH, there is an urgent need for new interventions that target EBI to potentially attenuate the secondary injury from DCI and thereby improve the neurological and the overall clinical outcome [9–12, 15, 16].

This study has multifold theoretical and clinical premises to assess the extent of neuroprotection. Firstly, at a pathophysiological level, it has been demonstrated that xenon targets multiple processes implicated in the development of brain injury after aSAH, such as glutamate-mediated excitotoxicity, neuro-apoptosis, ischemia-reperfusion injury, and oxidant injury [9, 12, 16, 30, 64–69]. Secondly, multiple experimental animal models have demonstrated xenon’s neuroprotective effect on global ischemia, focal occlusive stroke, TBI, and SAH with functional and histopathological long-term benefits on the outcome [20–24, 26–37]. Furthermore, [name] et al. showed that xenon was able to decrease the global and regional cerebral metabolic rate of glucose (MRGlu) using positron emission tomography (PET) in healthy human volunteers [70, 71]. Additionally, the Xe-Hypotheca trial was a proof-of-concept study and the first to demonstrate xenon’s ability to attenuate the extent of a white matter injury after global ischemia, mainly due to a protective effect on myelin [43]. A white matter injury is common after an aSAH during the first 72 h after ictus and has an independent predictive value for DCI and the neurological outcome, this explains why the results of the Xe-Hypotheca trial are particularly relevant [44, 72–75]. Good white matter function is fundamental for normal neurocognitive performance. Since as many as 75 % of survivors will experience psychosocial, neurocognitive, or other neurological problems, there is a clear target population of individuals who could benefit from xenon’s putative neuroprotective effect. It is also important to note that the white matter injury after SAH has been observed with fractional anisotropy, a technique that is known to reflect axonal injury and demyelination [44, 72–80]. For that reason, the fractional anisotropy will be the primary endpoint of this study.

As a secondary endpoint of the Xe-HypotheCA trial, inhaled xenon combined with mild therapeutic hypothermia resulted in a reduced myocardial injury when compared to that achieved by hypothermia alone as demonstrated by the significantly lower release of troponin-T from baseline to 72 hours after OHCA in the xenon group. The incremental change of troponin-T was also associated with higher mortality at six months [40]. In addition, the Xe-Hypotheca trial revealed that inotropic support with norepinephrine during the first 72 h after cardiac arrest was 84.3% higher in the control group than in the patients treated with xenon. Among aSAH patients, 35% displayed elevations of troponin I, 35% experienced arrhythmias, and 25% exhibited ventricular wall motion abnormalities with a catecholamine-induced process proposed to be the most plausible mechanism behind the cardiac complications [5, 81–84]. It is known that the cardiac manifestations, which usually persist for 1–3 days, are more common in patients who will later develop DCI, and these are associated with worse outcomes. A clinical syndrome termed Neurogenic Stress Cardiomyopathy (“stunned myocardium”) may contribute to death in 12% of aSAH patients. It is also well-documented that high levels of catecholamines associate with cardiac dysfunction, late vasospasm, and poorer outcome [85–91]. Therefore, xenon’s cardioprotective and inotrope-sparing effects may prove to be beneficial after an aSAH.

The start of the trial has been postponed due to the respirator shortage caused by the corona pandemic, but it is now expected to start during 2023. Patient recruitment will start initially (i.e., a feasibility period of 3–6 months) in Turku University Hospital, with Tampere and Kuopio University Hospitals joining in at a later stage after the feasibility period. Patient recruitment is expected to last four (4) years and the neurological follow-up surveys will require an additional two (2) years. A feasibility study will be published, once 30 patients have successfully gone through the randomization process and received treatment. One of the main endpoints of the feasibility study is to demonstrate the safety of xenon when assessing ICP.

Due to the devastating nature of an aSAH, there is an urgent need for new neuroprotective strategies to reduce both the mortality and morbidity that are associated with aSAH. In this respect, this study aims to deliver new interventional strategies for the treatment of aSAH.

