## Sample size {14}

A sample size of 100 is estimated on the basis of recent studies in aSAH patients as being able to provide 80% power with a 2-sided α level of 0.05 in order to detect a mean difference of 0.02 (SD 0.035) in the global fractional anisotropy of white matter between the xenon-treated group and the control group [44]. In addition, this mean difference is estimated to have a predictive value for DCI and poor neurological outcome. It is estimated that approximately 30% of the enrolled patients will be lost from the MRI studies, and therefore, 80 patients per group will be enrolled in this study.

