### Interim analyses {21b}

No interim analysis will be performed. However, an interim analysis can be performed if requested by the safety board, e.g., should early termination of the trial be considered due to a suspicion of compromised patient safety by xenon or by other reasons.

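### The plan rules out interim analyses other than at the safety board's request, yet schedules a mid-recruitment publication on xenon's ICP safety after 30 patients

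*Protocol article*

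**What the plan says.** Under Interim analyses {21b}, the protocol article states "No interim analysis will be performed". It makes one exception: "However, an interim analysis can be performed if requested by the safety board". The example given is early termination considered "due to a suspicion of compromised patient safety by xenon or by other reasons".

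The Discussion commits to something else: "A feasibility study will be published, once 30 patients have successfully gone through the randomization process and received treatment". It adds: "One of the main endpoints of the feasibility study is to demonstrate the safety of xenon when assessing ICP". The interim-analysis section does not mention this report.

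Other sections that bear on the point:

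- Secondary outcome measures lists ICP level, need for ICP therapy and duration of ICP therapy, each up to 14 days.
- Sample size {14} says "80 patients per group will be enrolled in this study".
- Recruitment {15} and Implementation {16c} describe the feasibility period as the opening stage of this trial at Turku, with Tampere and Kuopio joining later. Nothing sets the early patients apart from the 80 per group.
- Who will be blinded? {17a} says that the attending teams cannot be blinded during the intervention.
- The data monitoring committee section {21a} provides for an independent Data and Safety Monitoring Board with its own plan.

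**The concern.** The report is triggered by a patient count, not by the board, so the stated exception does not cover it. An analysis of a trial outcome in trial patients, made and published before recruitment ends, is an interim analysis whatever its title. The two sections therefore cannot both stand as written.

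The main risk is the release of comparative data. The teams who treat ICP know the allocation. Published ICP results by arm from this very trial could shift how they co-treat, whom they approach and how relatives respond to a consent request. Blinded reading of the scan protects the measurement of the primary outcome. It does not protect the composition or treatment of the patients enrolled afterwards.

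There is also a risk in the claim. A report set up to demonstrate safety in so few patients may give false reassurance, or false alarm, to the public and to the trial's own sites.

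**Working it through.** **1. The plan's own sample size.** Inputs from Sample size {14}: difference 0.02, SD 0.035, two-sided α 0.05, power 80%.

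- Normal approximation: n per arm = 2 × (1.960 + 0.842)² × (0.035/0.02)² ≈ 48.1, rounded up to 49.
- The t-based solution is 49.05, so 50 per arm and 100 in total, with power 0.81. The stated 100 is reproduced.
- Allowance for 30% MRI loss: 50/0.7 = 71.4, so 72 per arm. The plan enrols 80 per arm, 160 in total. The denominator of 160 is sound.

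**2. Share of the trial in the early report.** The trigger can be read in two ways.

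- 30 patients over both arms: 30/160 = 18.75%, about 15 per arm at 1:1.
- 30 xenon-treated patients: about 60 randomised, 60/160 = 37.5%.

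**3. Timing.** Recruitment {15} gives 20, 20 and 10 patients per year, 50 in all or 4.17 per month. The feasibility period at Turku alone is 3 to 6 months, which yields 20 × 3/12 = 5 to 20 × 6/12 = 10 patients. The 30-patient report therefore comes after that period.

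| Milestone | Other sites join at month 3 | Other sites join at month 6 |
|---|---|---|
| 30 patients | 3 + 25/4.17 = 9.0 | 6 + 20/4.17 = 10.8 |
| 60 patients | 3 + 55/4.17 = 16.2 | 6 + 50/4.17 = 18.0 |
| 160 patients | 3 + 155/4.17 = 40.2 | 6 + 150/4.17 = 42.0 |

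At Turku alone, 30 patients take 30/20 × 12 = 18 months. The plan expects recruitment to last 48 months. On either reading the trigger falls well before recruitment closes.

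**4. Precision for ICP.** The documents give no SD for ICP, so the result is in SD units.

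- 15 per arm: half-width = t(0.975; 28) × √(2/15) = 2.048 × 0.365 = 0.75 SD. With assumed SDs of 4, 6 and 8 mmHg this is 3.0, 4.5 and 6.0 mmHg. The difference detectable with 80% power is about 1.06 SD.
- 30 per arm: t(0.975; 58) × √(2/30) = 2.002 × 0.258 = 0.52 SD.

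**5. Precision for a harm with no observed events.** One-sided 95% upper limit = 1 − 0.05^(1/n).

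- n = 15: 1 − 0.05^(1/15) = 18.1%.
- n = 30: 1 − 0.05^(1/30) = 9.5%.

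**The case against.** Several objections deserve weight.

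**By-arm reporting is not stated.** This is correct. The Discussion does not say that arms will be compared, and the report could be pooled or confined to xenon patients. Still, a declared aim of showing xenon's safety in a 1:1 randomised sample points to a comparison. This remains an inference.

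**Care teams already see ICP by arm.** They are unblinded, every patient has ICP monitoring, and the ICP target is the same in both arms. Publication would add an aggregated, seemingly authoritative result, visible across sites and to those seeking consent. The resulting bias is plausible but cannot be quantified. The assessors of imaging and neurological outcome remain blinded.

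**Review at the safety board's request is ordinary.** It is, and it is not criticised here. Its details may properly sit in the separate monitoring plan.

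**A stronger reading is tempting.** A reader might infer from "due to a suspicion of compromised patient safety by xenon or by other reasons" that an efficacy look is allowed while the final test stays at 0.05, so that type I error is inflated. The text does not support this. The closing words can be read as patient safety compromised by causes other than xenon, efficacy is not mentioned, and no early test of fractional anisotropy is described. No type I error inflation on the primary endpoint follows. What remains is loose wording that one sentence would settle.

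**Conclusion.** The concern holds as a contradiction between two sections and as an overclaim. A count-triggered publication on a listed secondary outcome is planned at 19% of enrolment (about 37.5% on the other reading), while the interim-analysis section allows no look except at the board's request. The sample is too small to demonstrate ICP safety: a half-width of about 0.75 SD with 15 per arm, and an upper limit of 18% (9.5% with 30 xenon patients) after no events.

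This rests on three assumptions: that the early patients count towards the 160, which nothing in the document contradicts; that accrual is near the stated rates; and, for the bias argument only, that results would be shown by arm. The contradiction itself does not depend on the third. The matter should be settled before the 30-patient report, because publication cannot be undone.

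**What to change.** Reconcile Interim analyses {21b} with the Discussion.

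- In {21b}, declare the 30-patient look. State its endpoints, who sees the results, whether 30 counts both arms or xenon-treated patients only, and that the primary endpoint is not examined.
- Limit the mid-trial publication to pooled feasibility and process measures, such as consent rate, time from onset to randomisation and to xenon, completeness of xenon delivery, and MRI completion.
- Send by-arm ICP and other safety data only to the independent board named in {21a}. Publish them once recruitment and primary data collection have closed.
- In the Discussion, replace the aim of demonstrating safety with describing it.
- In {21b}, clarify the closing words of the exception by stating that the trial will not be stopped early for efficacy on such a look. The board's freedom to request a review on other grounds need not be narrowed.

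The cost is wording in two sections and later publication of by-arm ICP data. No extra patients or measurements are needed, and no clinical rule changes.

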## Trial status

Recruitment for the trial is expected to begin in Turku University Hospital on the 1st of October 2023. The two other research sites in Finland, Tampere and Kuopio University Hospitals, are expected to join once the feasibility of the protocol has been assured. The estimated date for finishing the recruitment phase is October 2027.

## Data Availability

The data of this study will be available to investigators whose proposed use of the data has been approved by an independent review committee. The individual participant data that underlie the results can be shared (text, tables, figures, and appendices), after de-identification, along with the study protocol and after publication. These data will be available at 6 months after the publication and will be available for 12 months from publication. Data can be used for individual participant data meta-analysis. Requests and proposals should be directed to [contact]. In order to gain access, data requestors will need to sign a data access agreement.

## Abbreviations

AE: Adverse events
CBF: Cerebral blood flow
CDE: Clinical data element
CPP: Cerebral perfusion pressure
CT: Computer tomography
CTA: Computer tomography angiography
DCI: Delayed cerebral ischemia
DSA: Digital subtraction angiography
DTI: Diffusion tensor imaging
EBI: Early brain injury
EVD: External ventricular drainage
FI02: Fraction of inspired oxygen
FA: Fractional anisotropy
ICP: Intracranial pressure
ICU: Intensive care unit
MAC: Minimal alveolar concentration
MR: Magnetic resonance
MRA: Magnetic resonance angiography
NMDA: N-Methyl-D-aspartate
NFL: Neurofilament light chain
NSE: Neuron-specific enolase
PEEP: Positive end-expiratory pressure
PET: Positron emission tomography
SAE: Serious adverse event
SAH: Subarachnoid hemorrhage
aSAH: Aneurysmal subarachnoid hemorrhage
SUSAR: Suspected unexpected serious adverse reaction
TnT: Troponin-T
TOF: Time-of-flight
Xe: Xenon
